#### 2.5.2. Pain evaluation.

This is the secondary outcome of the study and it will be assessed at baseline and after the 12 weeks of treatment. Pain will be evaluated using a visual analog scale (VAS). It is a subjective scale to measure the intensity of pain, described by the patient. The child is asked to mark the intensity of the pain on a corresponding linear scale from 0 to 10, taking 0 without pain and 10 extreme pain. The point indicated by the patient is the intensity.^[10,12]^

### 2.6. Randomization

To randomly distribute the individuals in the experimental groups, a random sequence generator (https://www.randomizer.org/tutorial/) will be used. Opaque envelopes will be identified with each number and inside it a sheet containing the information of the corresponding experimental group will be inserted. The envelopes will be sealed and kept in a safe place until the time of the procedures. The generation of the sequence and the preparation of the envelopes will be performed by a person who is not involved in the study.

### 2.7. Interventions

#### 2.7.1. ILIB therapy protocol.

Participants will receive the ILIB treatment for 20 minutes. The laser to be used is infrared-red, with power of 100 mW ± 20%, wavelength 808 nm ± 10 nm, continuous application.^[13]^ These parameters were taken as a reference since they were presented in a previous article, in which it was considered safe and did not cause discomfort to the patients. The technique is not invasive, the point of irradiation is by continuous and direct transcutaneous application to the radial artery by means of a bracelet that inserts the laser beam. Two sessions of 20 minutes will be conducted per week, for 12 weeks.

Study participants will undergo 2 phases of collection. The first, called the Control Phase, in which the individuals are evaluated, and will remain for a week without any physical and/or dental intervention, followed by a new evaluation and the start of the second phase, called the Treatment Phase, in which individuals will be assigned to one of three research groups.

#### 2.7.2. Groups.

•Group 1 ILIB (n = 15): Participants will be subjected to ILIB protocol sessions. It is a noninvasive technique that consists of a low-intensity laser that is attached to a bracelet that has been developed so that the light beam is transported transcutaneously over the radial artery.^[12]^ They will receive 2 sessions per week for 12 weeks, and will be reassessed 1 month after the end of the proposed therapy.•Placebo Group (n = 15): Participants will be treated in the same way as the ILIB group. The person in charge of the ILIB application will simulate the irradiation with the equipment kept off. So that the participant does not identify the group to which he/she/they belong, the device activation sound (beep) will be turned on at the time of application. They will receive 2 sessions per week for 12 consecutive weeks.•Control Group (n = 15): Composed of individuals who will not receive any type of intervention. Before the procedure and 1 month after the end of therapy, pain will be assessed using the VAS and the opening and closing movement will be measured with a digital caliper.

### 2.9. Blinding

The clinical evaluations will be performed by examiners blinded to the groups to which each participant belongs. Unblinding is not permitted.

### 2.10. Sample size calculation

Sample calculations were performed using a significance level of 0.05 (which implies a type I error of 5% and will result in an analysis with a 95% confidence interval) and an absolute error of 5%. Considering a loss of 10%, a loss of 1.5 participants per group should be predicted, so 45 participants will be recruited, 15 per group.

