### 2.11. Statistical analysis

The data will be tabulated and processed using the G Power version 3.1.9.2 program. The values will be tested for normality by the Kolmogorov–Smirnov test, and will be expressed as mean and standard deviation if Gauss curve is assumed. For the comparison between the groups, the T test will be carried out, considering a level of significance of 0.5% (*P* < .05). No loses greater than 5% of the sample are expected.

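### The sample size of 45 rests on a 5% precision criterion that does not match the planned between-group t tests, and 45 cannot be reproduced from the stated inputs

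*Protocol article*

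**What the plan says.** Section 2.10 of the protocol article begins "Sample calculations were performed using a significance level of 0.05" and adds that this "will result in an analysis with a 95% confidence interval) and an absolute error of 5" per cent. It then allows for attrition and concludes: "Considering a loss of 10%, a loss of 1.5 participants per group should be predicted, so 45 participants will be recruited, 15 per group". These are the only inputs given. The section names no formula, expected proportion, population size, power, effect size or standard deviation.

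Section 2.11 describes a comparative analysis: "For the comparison between the groups, the T test will be carried out". There are three randomised groups (ILIB, placebo, no treatment). The same section gives a different figure for attrition: "No loses greater than 5% of the sample are expected".

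**The concern.** A confidence level with an absolute error answers the question of how precisely one quantity will be estimated. This trial asks whether randomised groups differ, and its sensitivity depends on the size of the difference, the spread of the outcome, the significance level and the power. The criterion in Section 2.10 therefore does not address the comparison in Section 2.11, and under ordinary inputs it does not lead to 45 or 15 either.

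The stake is interpretation. A reader who takes the 5% at face value may think the trial is precise, when 15 per group can reliably detect only large differences. A non-significant result could then be over-read as evidence that ILIB has no effect.

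**Working it through.** **Inputs from the article.** Significance level 0.05 with 95% confidence (z = 1.96), absolute error 0.05, loss 10%, N = 45 as 15:15:15 (all Section 2.10); between-group t test, and loss of at most 5% (Section 2.11).

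**Assumptions of this check.** The estimate is a proportion p, or alternatively a mean on the 0–10 VAS. Power is 80% and tests are two-sided at 5%.

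**1. The plan's own loss arithmetic.** 15 × 0.10 = 1.5 and 13.5 / 0.9 = 15. This part is consistent. It leaves 13.5 per group, or 13 whole children.

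**2. Attempt to reproduce 45 or 15 as precision for a proportion.** n = 1.96² × p(1 − p) / 0.05².

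| p | n |
|---|---|
| 0.5 | 384 |
| 0.2 | 246 |
| 0.1 | 138 |
| 0.05 | 73 |
| 0.03 | 44.7 |
| 0.01 | 15.2 |

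The formula is symmetric in p and 1 − p. So 45 needs p near 3% or 97% (near 2.7% or 97.3% if the target is 40.5 before loss), and 15 needs p near 1% or 99%.

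**3. Finite-population correction.** n = 384.1 / (1 + 383.1 / N_pop), at p = 0.5.
- N_pop = 51: 384.1 / 8.51 = 45.1.
- N_pop = 45: 384.1 / 9.51 = 40.4, and 40.4 / 0.9 = 44.9 after allowing for loss.

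**4. Precision that the design gives.** Half-width = 1.96 × √(p(1 − p) / n), at p = 0.5.
- n = 45: 14.6 points.
- n = 15: 25.3 points.

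These are about three to five times the stated 5.

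**5. Alternative reading: 5% of the 0–10 VAS, that is ±0.5.** n = (1.96 × SD / 0.5)². This gives 15.4 at SD 1 and 61 at SD 2. The article states no SD.

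**6. What the planned comparison can detect.** Two-group t test, n per group, noncentral t with 2n − 2 degrees of freedom and noncentrality d√(n/2), solved for 80% power.

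| n per group | Two-sided 5% | 5% split over three pairwise tests |
|---|---|---|
| 15 | 1.06 SD | 1.25 SD |
| 13 | 1.15 SD | 1.35 SD |

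At two-sided 5%, power for a difference of 0.8 SD is 56% with 15 per group and 50% with 13. For 0.5 SD it is 26% and 23%.

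**The case against.** The strongest reply is that Section 2.10 names no formula, so a single-proportion calculation is an inference, and the figure of 384 depends on p = 0.5, which is not in the article. That stands, and both are labelled above as assumptions.

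A reader might infer that the justification is simply false, or that its inputs cannot give 45. The article does not support that. The stated inputs leave N undetermined, and steps 2 and 3 show unstated values that would yield 45. They look unlikely: every enrolled child has TMD, the Discussion calls TMD highly prevalent without giving a figure, and a finite-population correction belongs to a survey of a closed group. They cannot be excluded, however. Even so, they would describe the precision of one pooled estimate and not the sensitivity of a comparison between groups.

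A reader might also infer that the size was fixed by feasibility. No section says so; Section 2.4 says only that patients already attending the clinic will make recruitment easier.

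Nor do two neighbouring statements show that N is wrong. A 10% planning allowance beside an expectation of at most 5% can be read as a safety margin, although the wording should agree. And "The data will be tabulated and processed using the G Power version 3.1.9.2 program" concerns the choice of analysis software.

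Finally, an article may leave details to a fuller protocol. Missing inputs alone would not be a point. The point is that the criterion actually stated is of the wrong kind for the analysis actually stated.

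**Conclusion.** The concern holds in this limited form: the sample size cannot be reproduced from the stated inputs, and those inputs form a precision criterion that does not fit the planned between-group tests. The 5% is not delivered under ordinary readings. It is missed by a factor of about three to five if the estimate is a proportion near 0.5, and it holds for 15 children on the VAS only if the SD is about 1.

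The detectable differences rest on several choices:
- The outcome is continuous (VAS or mouth-opening range). They do not apply to the diagnostic categories of the RDC/TMD, which is the primary outcome.
- Power is 80%, which the article does not state.
- The significance level is 5%. Section 2.11 writes 0.5% beside P < .05, and 5% is taken here because Section 2.10 gives 0.05.
- Section 2.11 names no key contrast among the three groups, so the figures with and without the three-way split are both shown.

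The defect lies in the stated rationale. It does not by itself show that more children must be recruited.

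**What to change.** In Section 2.10, either delete the claim of a 5% absolute error or supply the inputs that in fact gave 45 (the quantity estimated, its expected value, and any population size). In both cases, add what the design delivers for the planned comparison. For example: for a continuous outcome, a two-sided 5% two-group t test has 80% power for a difference of about 1.06 SD with 15 per group, and about 1.15 SD with 13 per group after 10% loss; if the 5% is split over three pairwise tests, these become about 1.25 and 1.35 SD. Do not state a feasibility basis unless the sponsor confirms it. Use one loss figure in Sections 2.10 and 2.11.

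The change is to wording only, and no patients are added. The cost is that the stated sensitivity becomes visibly less favourable.

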### 2.11. Statistical analysis

The data will be tabulated and processed using the G Power version 3.1.9.2 program. The values will be tested for normality by the Kolmogorov–Smirnov test, and will be expressed as mean and standard deviation if Gauss curve is assumed. For the comparison between the groups, the T test will be carried out, considering a level of significance of 0.5% (*P* < .05). No loses greater than 5% of the sample are expected.

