## Abstract

**Methods::**

This will be a blind, randomized, and controlled clinical trial, which will be carried out on children between 6 and 12 years of age who enter the Catholic University of Uruguay, Faculty of Health Sciences, Postgraduate School, for treatment. To be included, children must present temporomandibular disorders, based on the diagnostic criteria will be the Research Diagnostic Criteria for Temporomandibular Disorders (RDC/TMD). Forty-five participants will be randomized to three groups: Group 1—ILIB with 2 sessions of 20 minutes for 12 weeks (n = 15); Group 2—Placebo laser application with 2 sessions of 20 minutes for 12 weeks (n = 15); Group 3—Control with no treatment (n = 15). Irradiation will be performed by continuous and direct transcutaneous application to the radial artery, by means of a bracelet that inserts the laser beam. The laser to be used is infrared, power 100 mW ± 20%, wavelength 808 nm ± 10 nm, continuous application. RDC/TMD and pain evaluated through a visual analog scale will be the outcome measures.

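### Three arms are to be compared by t-test with no main comparison named, at a significance level written two ways, so a contrast with the untreated arm could carry the efficacy claim

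*Protocol article*

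**What the plan says.** - **Design.** The Abstract states: "Forty-five participants will be randomized to three groups". Section 2.10 gives the sizes: "so 45 participants will be recruited, 15 per group".
- **Test.** Section 2.11: "For the comparison between the groups, the T test will be carried out". It names no pair, overall three-group test, testing order or adjustment. The aim at the end of the Introduction names no comparator.
- **Level.** The same sentence of 2.11 goes on "considering a level of significance of 0.5" per cent, with P < .05 in brackets. Section 2.10 says: "Sample calculations were performed using a significance level of 0.05", and ties this to a 5% type I error and a 95% confidence interval.
- **Comparators.** In section 2.7.2 the placebo arm receives a sham, with the device off and its beep on. The control arm receives nothing.
- **Outcomes.** RDC/TMD is primary (2.5.1) and VAS pain secondary (2.5.2). On the VAS: "It is a subjective scale to measure the intensity of pain, described by the patient".
- **Blinding.** Section 2.9: "The clinical evaluations will be performed by examiners blinded to the groups to which each participant belongs".

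**The concern.** A two-group test applied to three arms becomes up to three pairwise tests per outcome. If each is judged at 0.05 and any one may be reported as the result, the 5% error rate given in 2.10 does not apply to the trial's conclusion.

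The choice of comparator matters more. ILIB versus placebo isolates the laser, because children in both arms attend the same sessions and hear the same beep. ILIB versus no treatment does not. Untreated children get no sham, so they know their allocation, and they miss 2 x 12 = 24 sessions. Expectation and attention are then mixed with any laser effect. A reported benefit could rest on that contrast even if ILIB did no better than sham.

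**Working it through.** **Inputs.** Three arms of 15 (2.10); t-test (2.11); level 0.05 (2.10, and P < .05 in 2.11) or 0.5% (2.11). Tests are taken as two-sided because 2.10 links 0.05 to a 95% interval. Assumed: normal data, equal variances, pooled t-tests.

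**1. The plan's own figures.** One pre-named test at 0.05 has a 5% false-positive rate, as 2.10 says. The loss allowance is consistent: 15 x 0.10 = 1.5, and 13.5 / 0.90 = 15. The base of 13.5 per arm cannot be derived, because 2.10 gives only the level "and an absolute error of 5" per cent and the loss. It gives no effect size, standard deviation (SD), power or outcome. The sample size therefore does not show which pair the trial was built around.

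**2. Error rate at 0.05, no true differences.** If the tests were independent:

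- two ILIB contrasts: 1 - 0.95^2 = 9.75%
- all three pairs: 1 - 0.95^3 = 14.3%

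The pairs share arms, so these are too high. Simulation (200,000 trials, 15 per arm) gives:

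| Tests counted, one outcome | Level 0.05 | Level 0.005 |
|---|---|---|
| ILIB vs placebo only | 5.0% | 0.5% |
| Two ILIB contrasts | 9.1% | about 1.0% |
| All three pairs | 12.2% | 1.4% |

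(The first row is the nominal level.) With 13 per arm, the two multi-test figures at 0.05 are again about 9% and 12%. If both outcomes are tested across all three pairs and given equal standing, the rate is 23.0%, 21.3% or 18.6% at 0.05 for assumed outcome correlations of 0, 0.5 or 0.8. At 0.005 it is 2.4% to 2.7%.

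**3. Which contrast carries the claim.** Assume the laser does nothing, but ILIB and sham children both score better than untreated children by d SD. The values of d are assumptions. Chance of a significant result with 15 per arm:

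| d | ILIB vs no treatment, 0.05 | ILIB vs placebo, 0.05 | ILIB vs no treatment, 0.005 |
|---|---|---|---|
| 0.3 | 12% | 5% | not computed |
| 0.5 | 27% | 5% | 6.3% |
| 0.8 | 56% | 5% | 22.1% |

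The 0.05 columns are simulated; the 0.005 column is exact t-test power. At 0.005 the ILIB versus placebo rate would be 0.5%, so the stricter level shrinks this problem without removing it.

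**4. Which outcomes are exposed.** VAS pain is marked by the child, so blinded examiners do not protect it. RDC/TMD is mixed. Its 31-item questionnaire covers facial pain history, and its diagnoses include myofascial pain and arthralgia. Its physical examination and caliper readings are made by blinded examiners.

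**5. Price of the alternatives.** Effect detectable with 80% power for one pair:

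| Approach | n = 15 per arm | n = 13 per arm |
|---|---|---|
| One named comparison at 0.05 | 1.06 SD | 1.15 SD |
| Bonferroni over three pairs, 0.05 / 3 = 0.0167 each | 1.25 SD | 1.35 SD |

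Bonferroni gives a familywise rate of 4.4%. Naming the comparison costs no alpha.

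**The case against.** **The level.** The rates of 9% and 12% need 0.05, and 2.11 also says 0.5%, at which every familywise figure above is below 5%. This stands as a qualification. The bracketed P < .05 and section 2.10 make 0.05 the better-supported reading, but the article contradicts itself.

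**Silence is not a decision.** Multiplicity rules are often left to an analysis plan, and none is shown here. A reader might infer that no adjustment will be made; the article supports only that none is stated. A t-test is also valid in a three-arm trial once a pair is named. What remains is that 2.11 fixes a two-group test and a threshold without saying which of two very different comparators answers the question.

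**Larger error rates.** A reader might infer a false-positive rate above 20%. That counts placebo versus no treatment, which cannot support an ILIB claim, and gives VAS pain equal standing although 2.5.2 calls it secondary. For an ILIB claim on one outcome the figure is about 9%.

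**Blinded examiners.** They do protect much of the primary assessment. It would go too far to say that lack of participant blinding undermines every ILIB versus no-treatment result. The objection fails for the VAS and the RDC/TMD questionnaire.

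**Conclusion.** The point holds in limited form. Section 2.11 fixes a two-group test for three arms and names no main pair. At 0.05 this gives about a 9% chance of at least one false-positive ILIB contrast on one outcome, and about 12% over all three pairs. These figures assume normal data, equal variances and each pair tested at the full level. The literal 0.5% would bring them below 5%, so the level must be reconciled.

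The open choice of comparator is a fault at either level. A reader might infer that the trial plans to claim success on ILIB versus no treatment. The article states no success rule, so it supports only that nothing prevents this. The 12% / 27% / 56% figures illustrate the risk under assumed non-specific effects; they do not predict it.

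**What to change.** In section 2.11:

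- State one level, two-sided 0.05, and remove the 0.5%.
- Name ILIB versus placebo as the primary comparison on the primary outcome.
- Test ILIB versus no treatment at 0.05 only if the primary comparison is significant. Report placebo versus no treatment as an estimate with a 95% confidence interval.
- Keep VAS pain secondary, as 2.5.2 has it, with ILIB versus placebo as its main contrast.
- State which RDC/TMD measure is compared, since 2.5.1 describes diagnoses, movements and a questionnaire without choosing one. If it is continuous, estimate all contrasts from one three-arm model with pooled variance.
- Reconcile the assessment time. Sections 2.5.1 and 2.5.2 place it after the 12 treatment weeks, whereas 2.7.2 describes assessment one month after treatment finishes.

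The testing rule takes a few lines and leaves arms, sessions and sample size unchanged; choosing the measure and reconciling the time take more thought. All of it must be settled before results are seen. The downside is that no formal claim against no treatment is possible if ILIB versus placebo fails. Pain, though listed first in the aim, would support only a secondary conclusion.

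### The between-group t-test is fixed with no response variable and no baseline adjustment; for pain and range of movement it is valid but less precise than ANCOVA on measurements already scheduled.

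*Protocol article*

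**What the plan says.** Section 2.11 names one comparison between groups: "the T test will be carried out". It states neither the response variable nor a covariate.

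Measurements before treatment are planned. On pain, section 2.5.2 says "it will be assessed at baseline and after the 12 weeks of treatment", and section 2.5.1 gives the same timing for RDC/TMD, whose examination includes range of movement by digital caliper. Section 2.7.1 adds a one-week Control Phase before treatment. In it the children are evaluated, then each "will remain for a week without any physical and/or dental intervention, followed by a new evaluation". That makes two evaluations before treatment, but the section does not list what is measured at the second one. Section 2.5 speaks of a single baseline. No section gives either evaluation a role in the comparison.

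On size, section 2.10 concludes "so 45 participants will be recruited, 15 per group".

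**The concern.** A t-test takes no covariate, so naming it as the comparison is a choice and not only a detail left open. The aim in the introduction concerns less pain and more movement, both of which plausibly depend on where the child started. With 15 per arm, the chance difference between two arms in mean baseline has a standard error of sqrt(2/15) = 0.37 SD, so about one comparison in three starts more than 0.37 SD apart. A t-test on final values carries that imbalance into the estimate in proportion to the baseline-outcome correlation. A t-test on change overcorrects for it when the correlation is low.

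Two things are at stake: precision in a trial with little to spare, and a choice left open until the data are seen. A change could be taken from either evaluation before treatment, and nothing says which one is the baseline.

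**Working it through.** **The plan's own figure.** The 15 per group cannot be reproduced. Section 2.10 gives a significance level, "an absolute error of 5" per cent and a 10% loss, but no power, effect size or SD. The stated loss of 1.5 per group is 15 x 0.10, and 13/0.90 = 14.4 rounds up to 15, but the 13 has no source. I therefore take 15 as given and ask what difference it can detect.

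**Inputs from the document.** n = 15 per arm (section 2.10). For the significance level, section 2.10 says "Sample calculations were performed using a significance level of 0.05", while section 2.11 has "considering a level of significance of 0.5" per cent in words and a P value below .05 in brackets. I use 0.05.

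**Inputs assumed.** Two-sided test, 80% power, equal SDs at baseline and 12 weeks (SD set to 1), and a baseline-outcome correlation r of 0.3 to 0.7. The document gives no value for r.

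**Variance v of the quantity compared:**
- t-test on the 12-week value: v = 1
- t-test on change: v = 2(1 - r)
- ANCOVA, one baseline: v = 1 - r²
- ANCOVA, mean of two baselines that also correlate at r with each other: v = 1 - 2r²/(1 + r)

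**Detectable difference.** For two arms, solve for d such that the noncentral t distribution, with noncentrality d x sqrt(15/2)/sqrt(v), gives 80% power. Degrees of freedom are 28, or 27 for ANCOVA. With v = 1 the result is 1.06 SD (the normal approximation, (1.96 + 0.84) x sqrt(2/15), gives 1.02). The other entries are close to 1.06 x sqrt(v); for example, change at r = 0.3 gives 1.06 x sqrt(1.4) = 1.25.

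| r | t, 12-week value | t, change | ANCOVA, one baseline | ANCOVA, mean of two |
|---|---|---|---|---|
| 0.3 | 1.06 | 1.25 | 1.01 | 0.99 |
| 0.5 | 1.06 | 1.06 | 0.92 | 0.87 |
| 0.7 | 1.06 | 0.82 | 0.76 | 0.69 |

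**Against a t-test on final values.** One-baseline ANCOVA cuts the variance by r²: 9%, 25% and 49%. As an equivalent sample size, 15/(1 - r²) = 16.5, 20 and 29 per arm.

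**Against a t-test on change.** The ratio (1 - r²)/(2(1 - r)) equals (1 + r)/2, so ANCOVA cuts the variance by 35%, 25% and 15%. The change-score test itself is worth 15/(2(1 - r)) = 10.7, 15 and 25 per arm.

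**Power for an assumed difference of 0.8 SD** (t on final values, t on change, one-baseline ANCOVA): 56%, 43%, 60% at r = 0.3; 56%, 56%, 68% at r = 0.5; 56%, 78%, 84% at r = 0.7.

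**Averaging two baselines.** The last column of the table is sensitive to its assumption. If the two baselines correlate at 0.8 with each other instead, r = 0.5 rises only to 0.5/sqrt((1 + 0.8)/2) = 0.53, and the detectable difference goes from 0.92 to about 1.06 x sqrt(1 - 0.53²) = 0.90 SD.

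**Sensitivity.** With 13 completers per arm, the range at r = 0.3 to 0.7 is 1.15 SD for the t-test on final values and 1.09 to 0.82 SD for one-baseline ANCOVA. At a level of 0.005 with 15 per arm, the t-test on final values detects 1.43 SD.

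**The case against.** The strongest reply is that section 2.11 does not say what the t-test compares. A reader might infer that it discards the baseline, but a t-test on change would use it. At r = 0.7 the gain from ANCOVA would then be from 0.82 to 0.76 SD, not from 1.06 to 0.76. This stands, and it is why both comparators are shown. It does not rescue the t-test, since ANCOVA is more precise than either form throughout the assumed range.

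Second, r is unknown. Section 2.4 speaks of treating before major pain symptoms, and section 2.4.1 requires no minimum pain score, so many VAS values may lie near zero, with a low correlation and a poorer linear fit. This also stands. At r = 0.3 the gain over final values is only 9% of variance, and near zero correlation adjustment gains nothing and costs a degree of freedom.

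Third, a reader might infer that chance imbalance biases the trial. It does not. Under randomisation the t-test is unbiased and its standard error already allows for such imbalance. The point is precision alone.

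Fourth, a reader might infer that pain and movement are certain to be measured twice before treatment. Section 2.7.1 does not list the instruments of the second evaluation, so this needs confirming.

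Fifth, response variable, covariates and baseline definition are often left to an analysis plan, and this is a condensed article. Their absence alone would not be a finding. But the article names a specific test, and that test cannot adjust.

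**Conclusion.** The point holds in limited form. For VAS pain and caliper range of movement, the named t-test is valid but less precise than ANCOVA on a baseline that the protocol already schedules. Over an assumed r of 0.3 to 0.7, the detectable difference with one-baseline ANCOVA is 1.01 to 0.76 SD, against 1.06 SD for a t-test on final values and 1.25 to 0.82 SD for one on change. The gain may be small or substantial, depending on a correlation that the document does not give and on which form of t-test is meant. These figures rest on equal variances, 80% power, two-sided 0.05 and 15 analysed per arm.

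A reader might infer that this repairs the primary analysis. It does not. Section 2.5.1 makes RDC/TMD primary, and its diagnostic groups and count of diagnoses per joint suit neither a t-test nor a linear ANCOVA clearly. Only the range-of-movement part of that examination is covered here.

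**What to change.** **Section 2.11.** For VAS pain and range of movement, replace the t-test by a linear model on the 12-week value, with arm as a three-level factor and the baseline value of the same measure as covariate. Report adjusted differences between arms with 95% confidence intervals.

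**Section 2.5.** Define baseline as the mean of the two Control Phase evaluations if both include the measure, and otherwise as the single value before treatment. The main gain comes from adjusting at all; averaging may add little.

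**Section 2.7.1.** State which instruments are used at the second evaluation.

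**Time point.** The 12-week value follows section 2.5. Section 2.7.2 also places measurement of pain and opening one month after therapy ends, so the two sections should be reconciled before the response variable is fixed.

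**Cost.** One degree of freedom and a change of wording. With the single baseline no further data are needed. The mean of two needs none only if the second evaluation already includes the measure. The analysis of the RDC/TMD classification must be specified separately.

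### Section 2.11 gives the significance level as 0.5% and as P < .05 in one sentence; very probably a slip for 5%, but it sits in the only stated decision threshold

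*Protocol article*

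**What the plan says.** Section 2.11 (Statistical analysis) names the test: "For the comparison between the groups, the T test will be carried out". The same sentence then gives the threshold, "considering a level of significance of 0.5% (*P* < .05". This is the only place in the article where a cut-off for the analysis is set.

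Section 2.10 (Sample size calculation) gives the level used for planning: "significance level of 0.05 (which implies a type I error of 5% and will result in an analysis with a 95% confidence interval". It ends with the recruitment target, "so 45 participants will be recruited, 15 per group".

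**The concern.** The percentage and the P cut-off should be two ways of writing one number, and they are not. The sentence that decides whether a difference between groups is declared therefore carries two thresholds. Its percentage also disagrees with the level on which the sample size was planned.

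Taken word for word, a result of p = 0.02 passes the bracketed cut-off and fails the percentage. In a trial with 15 children per group, p-values in that range are quite plausible. A prespecified threshold should not leave a later reader to work out which of its two halves was meant.

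**Working it through.** **1. The stated figure.** 0.5% = 0.5/100 = 0.005. The bracket gives 0.05. The ratio is 0.05/0.005 = 10, so the two halves of the sentence do not agree.

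**2. Comparison with section 2.10.** The significance level there is 0.05. The type I error of 5% is 5/100 = 0.05. The 95% confidence interval corresponds to 1 − 0.95 = 0.05. All three agree with the bracket in section 2.11, and none agrees with 0.5%.

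**3. Could 0.005 be a derived level?**
- Halving for one side of a two-sided test: 0.05/2 = 0.025, not 0.005.
- Bonferroni over the three pairwise comparisons of three groups: 0.05/3 = 0.0167, not 0.005.
- The article mentions no multiplicity adjustment, and no other reason for a stricter level.

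**4. What the gap amounts to (illustration).** The inputs are as follows.
- From the article: a t test between groups (section 2.11) and 15 recruited per group (section 2.10).
- Assumed here: a two-sided test, all 15 per arm completing, and an outcome that can be expressed in SD units. The article states no sidedness, effect size, SD or power.

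With two arms of n = 15, df = 2 × 15 − 2 = 28. The smallest observed standardized difference that reaches significance is t_crit × √(2/n), with √(2/15) = 0.365. Power comes from the noncentral t distribution with noncentrality d × √(n/2). At d = 0.8 this is 0.8 × √7.5 = 2.19.

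| | level 0.05 | level 0.005 |
|---|---|---|
| Critical value of t, 28 df | 2.048 | 3.047 |
| Smallest significant observed difference | 2.048 × 0.365 = 0.75 SD | 3.047 × 0.365 = 1.11 SD |
| Power at a true 0.8 SD | 56% | 22% |
| Power at a true 1.0 SD | 75% | 40% |
| Difference detectable with 80% power | 1.06 SD | 1.43 SD |

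Observed differences between about 0.75 and 1.11 SD are significant at one level and not at the other.

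**5. Sensitivity to losses.** Section 2.10 allows for 10% loss: 15 × 0.10 = 1.5 per group, which leaves 13.5.
- With 14 completers per arm, the smallest significant differences are 0.78 and 1.16 SD, and power at 0.8 SD is 53% and 20%.
- With 13 completers per arm, they are 0.81 and 1.21 SD, and power is 50% and 18%.

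The gap stays about the same. The contradiction itself depends on none of the assumptions in steps 4 and 5.

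**The case against.** The strongest reply is that the article itself shows which level is meant. Section 2.10 expresses it in three consistent ways, and the confidence-interval wording there refers to the analysis as well as to the sizing. The bracket in section 2.11 gives the cut-off in the form in which it is applied to a p-value. Four expressions agree and one percentage stands alone. This stands: 0.5% is very probably a slip for 5%.

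A reader might infer more from the sentence than it supports, in three ways.

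- **That the decision rule is truly indeterminate, so that a result could be called either way afterwards.** The article does not support this. An analyst who used 0.005 to dismiss p = 0.02 would contradict both the bracket and section 2.10.
- **That the trial loses the power shown above.** It does so only if 0.005 is the real level, which nothing in the article suggests. The figures also rest on an assumed effect, sidedness and number of completers. The primary outcome in section 2.5.1 is the RDC/TMD, which includes diagnostic categories, so a standardized mean difference need not describe it. The figures show the distance between two levels; they do not measure harm to this trial.
- **That the correction should also fix a two-sided test and one primary comparison.** Section 2.10 does not state sidedness, and the article names no single primary contrast among its three groups. Those are separate questions, and this inconsistency does not settle them.

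The reply does not remove the contradiction. Section 2.10 describes the planning, while section 2.11 is the sentence against which the result will be checked. The text there is intact and wrong as written. This is not a detail left to a fuller document.

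**Conclusion.** The inconsistency is real: section 2.11 states two levels that differ tenfold, and its percentage conflicts with section 2.10. Read literally, p-values from 0.005 up to 0.05 get opposite verdicts. The intended level can be inferred as 5% with good confidence, so this is a necessary but small correction and not a flaw in the design. On the illustrative assumptions (two-sided t test, 15 completers per arm), the two levels differ by 0.75 against 1.11 SD in the smallest significant difference, and by 56% against 22% in power at a true 0.8 SD.

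**What to change.** In section 2.11, change 0.5% to 5% and leave the bracketed P < .05 as it is. The sentence then agrees with itself and with section 2.10. The cost is one number in the text; the test, the cut-off in the bracket and the 45 participants are unchanged. The correction should be made and dated before any results are known.

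If 0.005 was really intended, the bracket must become P < .005 and section 2.10 must be redone at that level, with the reason stated. That would cost far more. For illustration, by the normal approximation with an assumed 80% power and a true difference of 1.0 SD, the number per group is 2 × (1.960 + 0.842)² = 15.7, so 16, at 0.05. At 0.005 it is 2 × (2.807 + 0.842)² = 26.6, so 27.
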